### Sample size

Currently, no human studies have investigated the use of melatonin supplementation on hedonic eating. The proposed study is a pilot project; its main aim is to establish data for sample size calculations for a larger trial. Various studies recommend a total sample size of at least 24 participants for a two-arm trial [25]. Considering the sample size of previous studies on melatonin supplementation in overweight and obese Iranian women [26,27] and to increase the accuracy and power of the study, in this clinical trial, we plan to enroll 40 participants, which, with a 15% attrition rate, will increase to 46 subjects (23 in each group).

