### Blinding

The present pilot study is designed as a double-blind trial, ensuring that neither the researchers conducting the study nor the participants will know which group they have been assigned to. To maintain the double-blind nature, the packages containing melatonin and placebo tablets will be coded as ‘A’ and ‘B’ at the start of the study by an individual not involved in the research process. This coding serves to blind the researchers. Furthermore, the supplement and placebo pills will be made identical in color, shape, smell, and appearance to blind the participants.

Labels on the supplement packs will stay hidden until the study is finished. However, if any adverse events occur, unblinding is allowed according to the Medical Ethics Committee’s guidelines to determine whether the patient received melatonin or a placebo. If dropout rates reach 15% or higher due to adverse effects, we will conduct an intention-to-treat (ITT) analysis.

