### Intervention

Forty-six eligible women will be randomly assigned to either the melatonin group or the placebo group, with 23 participants in each group. Participants will take a 5 mg tablet one hour before bedtime with sufficient water and will be followed up for 8 weeks. The Tehran Darou Pharma & Food Supplement Company will supply the melatonin and placebo tablets, which will be identical in weight, size, shape, taste, color, odor, and packaging. Patients will receive the tablets during monthly study visits, with a total of three visits scheduled for the trial (before the intervention, after 1 month of intervention, and at the end of the intervention). Patients will be instructed on how to use their tablets and will receive weekly follow-up calls to improve response rates and fewer dropouts.

To enhance participant retention, the potential health benefits of melatonin will be explained, and the principal investigator will keep in regular contact with participants via phone calls.

Compliance will be assessed based on the number of unused tablets returned by each participant at the end of week four and the end of the trial. The remaining tablets will be counted to determine the total intake of the tablets. The total intake of tablets for each subject is calculated by subtracting the number of tablets unused from the number of tablets dispensed.

Participants can choose to leave the study at any point. Furthermore, the investigator has the authority to remove subjects from the study if they do not adhere to the protocol. Additionally, patients will be monitored for any adverse events following melatonin consumption. If any adverse events are attributed to melatonin, participants will be advised to discontinue the supplements and will be promptly referred to a specialist for further treatment.

It is important to note that no specific physical activity program, dietary recommendations, or regimens will be provided to the study subjects. Additionally, after considering the eligibility criteria, if subjects are being treated for any kind of disease during the study, they will not be deprived of routine treatment. Participants will receive either melatonin supplements or a placebo alongside their standard treatments.

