### Statistical analysis

Data will be analyzed statistically using SPSS 26.0 software, considering P values below 0.05 as indicative of statistical significance. The normality of data distribution will be checked using the Kolmogorov-Smirnov test, and an appropriate method will be applied to normalize variables that do not follow a normal distribution. Mean (standard deviation) and frequency (percentage) will be used to represent quantitative and qualitative variables, respectively. Independent sample t-tests will be used to evaluate differences in baseline means, while paired-sample t-tests will compare within-group differences. For variables assessed three times during the study (at the start, in the fourth week, and in the eighth week), a repeated measures ANOVA will be utilized. Additionally, Analysis of Covariance (ANCOVA) will assess the effects of the intervention between groups, adjusting for confounders such as baseline data and physical activity. In cases where dropout rates of 15% or more, an intention-to-treat (ITT) analysis will be performed. Missing data will be handled using multiple imputation methods.

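### Intention-to-treat analysis is conditional on 15% dropout, two sections word the trigger differently, and no analysis set is named below it

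*Protocol article*

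**What the plan says.** Two sections of the protocol article set a condition for the ITT analysis. Statistical analysis: "In cases where dropout rates of 15% or more, an intention-to-treat (ITT) analysis will be performed". Blinding: "If dropout rates reach 15% or higher due to adverse effects, we will conduct an intention-to-treat (ITT) analysis". The first counts dropout of any cause; the second adds a cause. No section says that ITT is run otherwise, and none names the population analysed when the condition is not met.

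Three other statements bear on this:

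- The Statistical analysis section adds, with no condition attached: "Missing data will be handled using multiple imputation methods".
- The Sample size section gives the attrition allowance: "we plan to enroll 40 participants, which, with a 15% attrition rate, will increase to 46 subjects (23 in each group".
- The Intervention section describes two routes by which women may stop. One is "the investigator has the authority to remove subjects from the study if they do not adhere to the protocol". The other is "If any adverse events are attributed to melatonin, participants will be advised to discontinue the supplements". It does not say whether data from these women are kept.

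**The concern.** Whether all randomised women are analysed as allocated should not depend on how many of them are lost. Here it does: ITT is an exception that is switched on by a result seen after randomisation. A reader has to infer what happens otherwise, and the natural inference is that some women without week-8 data may be left out.

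Losses in this trial could be related to treatment. The Harms section lists drowsiness, headache and dizziness with melatonin, and participants are told to stop the supplement for events attributed to it. If such women leave the analysis, the two arms are no longer the groups that randomisation formed. The Sample size section says that the main aim is to supply data for sizing a larger trial, so any bias would carry over into that design.

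The different wording of the trigger adds a second problem. For some patterns of loss, one section calls for ITT and the other does not.

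**Working it through.** **Inputs.** From the Sample size section: 40 participants wanted, 15% attrition, 46 randomised. From the Intervention section: 23 per arm. From the Statistical analysis and Blinding sections: threshold 15%, for any cause and for adverse effects respectively.

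**1. The plan's own figure.** 40 × 1.15 = 46.0, which reproduces the stated total. Dividing instead gives 40/0.85 = 47.06, or 48 with equal arms. Because 46 comes from multiplying, the loss that leaves 40 is 46 − 40 = 6, and 6/46 = 13.0%, not 15%.

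**2. When the any-cause trigger is met.** 15% of 46 is 6.9, so:

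- 6 losses: 6/46 = 13.0%, not met.
- 7 losses: 7/46 = 15.2%, met.

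The planned count falls one short of the trigger.

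**3. Where the two sections diverge.**

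| Losses, any cause | Of these, adverse effects | Statistical analysis | Blinding |
|---|---|---|---|
| 6 (13.0%) | any number | not met | not met |
| 7 (15.2%) | 3 (6.5%) | met | not met |
| 10 (21.7%) | 6 (13.0%) | met | not met |
| 7 (15.2%) | 7 (15.2%) | met | met |

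**4. How often each trigger would be met.** Assume that women drop out independently, and use the binomial distribution with n = 46.

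- True risk 15%: P(7 or more losses) = 0.546 and P(1 to 6 losses) = 0.453.
- True risk 13.0%: P(7 or more) = 0.393 and P(1 to 6) = 0.605.
- Blinding trigger, total risk 15%: if adverse effects cause 25%, 50%, 75% or 100% of losses (assumed shares), P(7 or more adverse-effect losses) = 0.002, 0.054, 0.256 or 0.546.

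**5. Possible bias if 6 women are left out.** Let D be the difference in mean week-8 outcome between dropouts and completers, in SD, the same in both arms. Let a and b be the numbers lost in the two arms. Leaving these women out shifts the between-arm difference by D × (a − b)/23. The documents give no D; 0.5 to 1.0 SD is assumed.

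| Split | (a − b)/23 | D = 0.5 | D = 1.0 |
|---|---|---|---|
| 3/3 | 0 | 0 | 0 |
| 4/2 | 0.087 | 0.04 | 0.09 |
| 5/1 | 0.174 | 0.09 | 0.17 |
| 6/0 | 0.261 | 0.13 | 0.26 |

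The zero in the first row holds only because D is taken as equal in both arms.

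**The case against.** A reader might infer that at the expected dropout this trial will report a completer analysis. The documents do not support that, for two reasons. The stated expected rate is 15%, which satisfies a trigger of 15% or more; only the planned count of 6 of 46 falls short. Also, no completer or per-protocol set is named anywhere, and the multiple-imputation sentence is unconditional, so it can be read as covering missing outcomes below the threshold too. Both points stand, and they limit the finding to an analysis set left unnamed. They do not rescue the rule: if imputation always kept every randomised woman in, the 15% condition would have no function.

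The conflict between the sections can also be softened. The Blinding sentence says if, not only if, and sits among remarks on adverse events. Any trial with 15% lost to adverse effects also has at least 15% lost overall, so that sentence could be a special case of the general rule. This reading is possible, but the protocol does not say which sentence governs.

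It would go too far to say that the investigators can simply choose their result. The threshold is fixed in advance and depends on dropout counts, not on outcomes. The discretion comes only from the two wordings and the unnamed set.

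Nor do the documents say that women who stop tablets leave follow-up, that removed women's data are discarded, or that removals count as dropouts. These points are open rather than settled the wrong way.

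**Conclusion.** The concern holds in this form: the protocol makes ITT conditional on observed dropout, words the condition in two ways that can disagree, and names no analysis set when it is not met. This is a stated rule, not a detail left to an analysis plan. It bears on every between-group comparison.

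The gap is not remote. The planned loss lies below the trigger, and with a true 15% risk per woman the any-cause trigger is missed, with at least one loss, in about 45% of trials.

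The size of any bias is not known from the documents. For 6 women left out it runs from 0 to 0.26 SD under the assumed 0.5 to 1.0 SD difference. The range 0.13 to 0.26 SD is the extreme in which all losses fall in one arm, and it should not be quoted as the expected bias.

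**What to change.** - Delete the 15% trigger in both the Statistical analysis and the Blinding sections.
- State that the primary analysis includes all randomised women in their allocated arm, whatever the dropout rate, with the multiple imputation already planned.
- State in the Intervention section that data from women who stop tablets or are removed are retained and analysed, and that their week-8 measurements are sought where they agree. This concerns data only; who stops or is removed is left as it is.
- Keep any completer or per-protocol analysis as a sensitivity analysis.

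The cost is a short amendment and a few extra week-8 contacts, including a fasting blood sample from women who have stopped. There is a limit to what this buys. The primary outcomes are measured only at baseline and at the end, so imputation from baseline would not remove bias if the loss is informative. Only the retained week-8 measurements can reduce that.

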### Confidentiality

Every participant will be assigned a unique identification code for data storage purposes. This code list will be accessible exclusively to researchers and safeguarded by the principal investigator during the trial. Participants’ personal information will be kept confidential in all published reports.

### Plans to give access to the full protocol, participant‑level data, and statistical code

The corresponding author will provide datasets, statistical code, and the full protocol upon reasonable request.

### Composition of the coordinating center and trial steering committee

The principal researcher coordinates the study, with regular communication among the study team and supervision by a steering committee. Additionally, the Ethics Committee at Tabriz University of Medical Sciences will monitor compliance with ethical guidelines, and the study will be revised or terminated if any ethical issues arise.

### Provisions for post‑trial care

Melatonin or placebo supplements will be given for 8 weeks. Once the trial is completed, routine care will continue.

### Dissemination plans

The final results and data will be shared in upcoming publications.

### Trial status

The recruitment process for the first phase of the project began on January 8, 2024, and is expected to be completed by October 1, 2024.

## Discussion

Despite the importance of hedonic eating in the context of overweight and obesity, there are limited interventions aimed at reducing it. In a study by Beaumont et al., transcranial direct current stimulation targeting the dorsolateral prefrontal cortex—known for its role in controlling hedonic eating—did not impact hedonic appetite when administered at 2 mA for 20 minutes [35]. However, another study found that intragastric quinine-hydrochloride infusion at a dose of 10 µmol/kg effectively reduced hedonic food intake and plasma ghrelin levels in non-obese women [36]. Additionally, an education-based intervention developed by Mason and colleagues successfully decreased the hedonic drive to eat in adults with obesity after 6 months [37]. Furthermore, thylakoid supplementation, taken once daily for 3 months, reduced the urge for palatable food in women with overweight [38]. In addition, the 12-week use of behavioral weight loss programs in adults with overweight/obesity resulted in a reduction in hedonic hunger, and this reduction was associated with better weight loss [16,39].

Melatonin is a hormone with antioxidant and anti-inflammatory properties. It also has a significant role in glycemic homeostasis, modulation of white adipose tissue activity, lipid metabolism, and mitochondrial activity. In addition, melatonin increases brown adipose tissue volume and activity [19]. A meta-analysis in 2021 showed that taking daily doses of melatonin of ≤ 8 mg leads to weight loss. Nevertheless, it has been noted that the mechanisms underlying weight loss with melatonin supplementation are intricate and not completely comprehended [18]. In addition to the mechanisms mentioned, according to the results of animal studies, it appears that melatonin may also impact body weight by reducing hedonic eating. Some animal studies have shown a decrease in the serum level of ghrelin in mammals after melatonin supplementation [20–22]. In zebrafish, melatonin supplementation decreased the expression of the ghrelin hormone gene, and the CB1 receptor gene expression, as well as food intake [7,23]. Furthermore, norepinephrine, which is essential for the production of melatonin at night, down-regulated levels of some endocannabinoids, within the pineal gland of rats [24]. As previously mentioned, endocannabinoids and ghrelin are involved in the hedonic eating process. Therefore, melatonin supplementation may probably reduce food intake and hedonic eating by decreasing the levels of endocannabinoids, the expression of the ghrelin hormone gene, the level of ghrelin, and the expression of the CB1 receptor gene. In conclusion, it appears that conducting a clinical trial to examine the impact of melatonin supplementation on hedonic eating intensity and related biochemical biomarkers in overweight or obese individuals may be beneficial.

### Strengths and limitations

This pilot study’s strengths lie in its use of a randomized, double-blind, placebo-controlled design to investigate the effects of melatonin supplementation on hedonic hunger intensity and related biochemical biomarkers in women with overweight/obesity, which is a novel approach. However, the research does have some limitations. Firstly, only two biochemical markers related to hedonic eating will be measured in this study. Secondly, despite employing a validated questionnaire for hedonic eating assessment, misclassification bias cannot be entirely eliminated. Lastly, despite accounting for potential changes in dietary intake or physical activity during statistical analysis, the participants’ self-reported dietary intake and physical activity could still influence the results. We anticipate that this trial will provide a general idea of the effectiveness of melatonin intervention in managing hedonic eating.
